## Abstract

**Background:**

Concepts for the nursing and care of cancer patients through a “navigation service” have attracted much interest. However, there is still room for improvement in terms of their funding and coverage. The Saxon Cancer Society designed a prospective, randomized, multicenter, longitudinal study with a view to determining the positive effects of a cancer patient navigator program. The objective of this ongoing study is to evaluate the impact of the cancer patient navigation program on cancer patients and cost bearers in Germany.

**Methods:**

The study population in this evaluation comprises cancer patients with gastric carcinoma, pancreatic carcinoma, colorectal cancer, melanoma or gynecological cancer who have been hospitalized at least once at one of the study centers as well as their relatives, outpatient and inpatient physicians, and cancer nurses. It is planned to randomize 340 cancer patients (stomach, colonic/rectal cancer, gynecological cancer, melanoma) at five centers to an intervention group (care by patient navigators based on standardized operating procedures) or a control group in a one-to-one ratio. The primary target parameter is the number of hospitalizations within the 12-month intervention period. The participants are asked to complete various questionnaires on patient-related outcomes at baseline and at 3 and 12 months (SF 36, HADS, PAM 13, and others). Data on drug therapy, utilization of health services, and medical expenses will also be analyzed.

**Discussion:**

For the first time, the study will provide data on the effectiveness of a patient support program in cancer care in Germany from a randomized trial with a high level of evidence.

**Trial registration:**

The study has been registered under DRKS00013199 in the German Clinical Trials Register.

## Background

The diagnosis of cancer has far-reaching and life-changing consequences for patients [1]. Despite the prevalence and paramount importance of cancer, our healthcare system is often inadequately prepared to address the needs of patients and their families in terms of psychosocial care, information provision, and coordination of necessary measures.

A patient navigation service for cancer patients was set up for the first time in the United States about fifteen years ago. Its aim was to provide timely access to high-quality care in a manner tailored to each patient [2–4]. The US National Cancer Institute extended the concept to include additional goals for selected cancer types, notably the improvement of patient satisfaction and cost effectiveness [5].

The qualification profile (medical training and/or nonmedical staff), the optimum duration of support [6], and the cancer patient navigation service activities required to meet the tasks at hand are still poorly standardized [7]. Only three randomized studies, all in the US and Canada, have so far been published on the effectiveness of the programs, and the results have been mixed [8–10].

In Germany, too, the data situation is very sketchy. However, an evaluation study on patient support of a health insurance fund with a quasi-experimental design which took into account various disease groups including cancer showed positive effects with regard to customer satisfaction, effectiveness/quality, efficiency, and system acceptance [11].

Against this backdrop, the Saxon Cancer Society (SKG) launched the “Onkolotse” cancer patient navigation program in 2009. It aims to provide healthcare professionals with effective support in their cancer-related work and to improve the care of cancer patients [12].

### Program description

“Onkolotse” cancer patient navigation program specialists are trained, SKG-certified nurses/carers, professionals, counselors, psychologists or social workers working in the field of oncology [13]. They are extensively trained in special self-paid courses that are divided into seven modules and comprise over 130 h of tuition. Training topics include issues relevant to cancer patients, in particular structures, processes, and contact persons in the management of the disease. The “Onkolotse” cancer patient navigator program stands for trustworthy information, support, and advice rooted in understanding and care, as well as psychological issues relating to cancer treatment [13]. Patients and their family members are assigned a skilled, permanent contact person to whom they can address their questions during the entire duration of cross-sectoral treatment and who also has the necessary time to devote to them. Care does not end with the acute phase of the disease but continues throughout rehabilitation and aftercare. Topics of the consultation can be, for example: which hospitals provide interventions or rehabilitation measures, what support services are available from authorities or health insurance funds (e.g. severe disability status, aids, rehabilitation), and who is able to provide outpatient aftercare. The knowledge gain, the support in developing or maintaining a positive attitude, and the teaching of problem-solving skills increase the individual’s health literacy and enable active, independent participation of the patient in the treatment process. Overall, continued support can help patients and relatives to cope better with a cancerous disease and to feel more at ease within the healthcare system.

### Objectives and hypotheses

The primary objective of this study is to evaluate the impact of the cancer patient navigation program on cancer patients and cost bearers in Germany. It is intended to provide decision-makers with helpful information that facilitates the transfer of the program to routine care.

#### Primary target parameter

The primary aim is to investigate changes in hospitalization rates of cancer patients.

The underlying hypothesis is that participation in the cancer patient navigation program is able to reduce the number of patients who need to be re-hospitalized within 12 months. The hospitalization rate (defined as at least one night spent in hospital within a 12-month follow-up period) is estimated to be 25% in the control group and 12.5% in the intervention group.

#### Secondary target parameter

The secondary target parameter is whether the control group and the intervention group differ in their HADS-D scores as a surrogate of psychological stress.

The underlying hypothesis is that the patients’ psychological burden is reduced by participation in the patient navigation project. Patients in the intervention group will have a lower level of anxiety and stress on the HADS-D scale compared to baseline (t1) and will have a lower level at three and 12 months compared to the control group.

#### Other secondary and explorative target parameters

Other target parameters will be compared between the intervention group and the control group. They include:The patients’ quality of lifeThe relatives’ quality of lifeThe psychological burden on relativesHealth status / general sense of healthSocial support / resources of patientsThe patients’ health literacyJoint decision-making between the patient and physicianDays absent from workThe waiting time for required treatmentsCompliance with treatmentsDouble testsSatisfaction with the treatmentsWorkflows / operational processesUse of servicesHealthcare costs

In addition, explorative analyses are planned, including analyses of the type of cancer and other patient-relevant variables.

## Methods/design

In line with the primary study objective, the design was chosen so that evidence of the effectiveness of the intervention can be generated at the highest possible level of evidence. The project was therefore designed as a prospective randomized, longitudinal, multicenter study. To our knowledge, no other RCT has been conducted in Germany on this topic. Other groups used a quasi-experimental design in which the control group was generated from insurance data [11]. A multicenter approach was chosen to obtain larger sample sizes and to ensure that the study optimally represents cancer centers. In addition, various types of cancer will be considered to assess the effectiveness of the program across multiple indications.

The program was implemented at five centers in Saxony, Germany. The evaluation also takes into account the network partners (office-based physicians) of the specialized hospitals, insofar as they contribute patients to the program.

Eligible patients are identified during their hospitalization in the participating centers and are informed about the study in a personal interview and with the help of written documents. If the patients give their written consent, they are randomized to the intervention group or the control group on a one-to-one basis. They are randomized with regard to the center, the type of cancer, gender, and age group. The following cancers are documented: pancreatic, gastric, colonic/rectal carcinoma, gynecological cancer and melanoma. While patients in the control group receive standard care, those in the intervention group are also in regular contact with their patient navigator.

The observation period in the intervention (cancer patient navigation program participation) and control (no cancer patient navigation program participation) groups is 12 months per patient. In this time period about 20 talks with the cancer patient navigation program specialists shall be held.

Figure 1 summarizes the study design and the times of data collection. A distinction is made between the recruitment phase, the inclusion phase, and the three survey dates during which data are collected. Exams are scheduled during hospitalization (t1), after three months (t2), and after twelve months (t3). The data are provided by the physicians at the hospitals, the participating office-based physicians, the relatives of the patients, and the cancer patient navigation program specialists (only in the intervention group). Secondary data used in the study include internal hospital statistics provided by the participating centers (medical controlling).

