### Inclusion criteria for patients

The patients must meet all of the following criteria to be included in the study:The patient is hospitalized at one of the five study centers.The patient has a diagnosis of gastric cancer, colonic/rectal cancer, pancreatic cancer, gynecological cancer, or melanoma.The patient has a cancer that falls into one of the following UICC TNM classifications:0 (t in situ, N0, M0)Ia (T1, N0, M0)Ib (T2, N0, M0)IIa (T3, N0, M0)IIb (T4, N0, M0)IIIa (every T, N1, M0)IIIb (every T, N2, M0)IV (every T, every N, M1)

or has a recurrent tumor or metastases (in the case of melanoma, also metastases that do not affect the skin).The patient is at least 18 years old.The patient has signed the written informed consent form.The patient participates in the study voluntarily.

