#### Covariables

The physician questionnaire records information on the type and stage of the cancer pursuant to the UICC TNM classification. In addition to patient questionnaires, demographic information is collected on, inter alia, age, gender, educational attainment, living conditions, work situation, migration background, work incapacity, and relationship status. Finally, patients are asked about any comorbidities based on a list of conditions.

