### Statistics

#### Sample size planning

The sample size planning is based on the primary endpoint, whose one-year incidence is estimated to be 25% in 2015 and 2016 according to data from the participating study centers. Based on earlier study findings, the case management program can halve the number of hospitalizations [11].

Thus, a hospitalization rate of 12.5% is expected in the intervention group. To illustrate this difference at a significance level of alpha = 5% and a statistical power of 80%, 152 patients per group are needed (chi^2^ test, normal approximation, PROC POWER SAS 9.4). Taking into account a dropout rate of 10% during the 12-month study period, a total of 170 patients per group, or 340 patients in total, are needed at baseline.

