#### Other secondary and explorative endpoints

Subgroup analyses are planned, especially in respect of the cancer type (indication), the cancer state, the cancer relapse status, and the presence of metastases.

In the addition, the following subgroups are evaluated:Patients in employment immediately after the cancer diagnosisPatients in employment after the first treatment, at the start of rehabilitationPatients of retirement age immediately after the cancer diagnosisPatients of retirement age after the first treatment, at the start of rehabilitation

Other analyses and possibly tests for statistical significance are specified in the statistical analysis plan.

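### The lead primary comparison ignores disease stage although entry runs from in-situ to metastatic disease; the test is valid, but precision is given away and a chance stage imbalance stays in the headline result

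*Protocol article*

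**What the plan says.** All references are to the protocol article.

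- **Who enters.** Inclusion criteria for patients lists stages from 0 (in situ) up to "IV (every T, every N, M1", and also admits recurrent tumors and metastases.
- **How they are allocated.** Methods/design: "They are randomized with regard to the center, the type of cancer, gender, and age group". Stage, relapse status and metastasis are not in that list.
- **What is recorded.** Covariables: "The physician questionnaire records information on the type and stage of the cancer pursuant to the UICC TNM classification".
- **What is analyzed.** The Primary endpoint paragraph under Statistics starts with a chi-square comparison of the share of patients with at least one night in hospital in the year. A second step then verifies the result with a linear model containing other factors, which are not named there.
- **Where stage reappears.** Subgroup analyses are planned "especially in respect of the cancer type (indication), the cancer state, the cancer relapse status, and the presence of metastases".
- **How it was sized.** The rate "is estimated to be 25% in the control group and 12.5% in the intervention group", and at a "significance level of alpha = 5% and a statistical power of 80%, 152 patients per group are needed" by chi-square test ("normal approximation, PROC POWER SAS 9.4").

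**The concern.** The endpoint is any overnight stay in 12 months, and under ITT-2 a death also counts as an event. Both can be expected more often in metastatic or recurrent disease than in early disease. The trial's own subgroup list suggests that its designers expect stage to matter.

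Stage is nevertheless controlled neither at allocation nor in the lead test. Balancing or adjusting for center, cancer type, gender and age group would still leave stage free to differ between arms within a cancer type. Two things are at stake:

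- **Interpretation.** If one arm happens to receive more advanced patients, the headline difference carries that excess, in either direction.
- **Precision.** A baseline value that is already collected, and probably prognostic, is not used where the result is decided.

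**Working it through.** **Step 1: the plan's own figure.** Inputs from Primary target parameter and Sample size planning: p1 = 0.25, p2 = 0.125, alpha 0.05 (taken as two-sided), power 0.80. With p̄ = 0.1875:

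n = [1.960·√(2·0.1875·0.8125) + 0.8416·√(0.1875 + 0.1094)]² / 0.125² = (1.0819 + 0.4586)² / 0.015625 = 151.9, so 152 per group.

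Allowing for dropout, 152/0.9 = 168.9, or 169; the article's 170 is consistent. The sizing is correct.

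**Step 2: how far stage can differ by chance.** The article gives neither the share with advanced disease (q) nor rates by stage, so both are assumed. I take q = 20–50% and an advanced-minus-early risk gap of 10–40 points, holding the control rate at 25%.

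- SD of the between-arm difference in advanced share = √(2q(1−q)/152), which is 4.6 points at q = 20% and 5.7 at q = 50%.
- Shift in the crude rate difference = imbalance × gap.

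**Step 3: does this invalidate the test?** The standard error of the crude difference is √(2·0.25·0.75/152) = 5.0 points with no effect, and √((0.1875 + 0.1094)/152) = 4.4 points under the planned effect. Random variation in stage mix is already inside those figures. In simulations of 40,000 trials per setting (stage left to chance), the crude chi-square rejected 5.0–5.2% of the time under no effect.

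**Step 4: shift and power under the planned halving of risk.**

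| Advanced share | Risk gap | Shift at 1 SD | Shift at 1.96 SD (share of 12.5) | Power, crude | Power, stage-stratified |
|---|---|---|---|---|---|
| 20% | 20 pts | 0.9 | 1.8 (14%) | 81.0% | 81.6% |
| 40% | 20 pts | 1.1 | 2.2 (18%) | 81.0% | 81.9% |
| 40% | 30 pts | 1.7 | 3.3 (26%) | 81.1% | 83.8% |
| 30% | 40 pts | 2.1 | 4.1 (33%) | 80.9% | 85.2% |
| 40% | 40 pts | 2.2 | 4.4 (35%) | 80.8% | 86.1% |
| 50% | 40 pts | 2.3 | 4.5 (36%) | 81.0% | 86.7% |

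The smallest case (20% advanced, 10-point gap) gives a 1.96-SD shift of 0.9 points (7%). With 20–40% advanced and a 35–50% risk in those patients, power of the stratified test runs from about 81% (20% advanced at 35% risk, the others at (25 − 7)/0.8 = 22.5%) to 86–87% (40% advanced at 50% risk, the others at (25 − 20)/0.6 = 8.3%).

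**Step 5: how often a large shift occurs.** At q = 40%, a shift of at least a quarter of the planned effect (3.1 points) has probability 0.5%, 6% and 16% for gaps of 20, 30 and 40 points. A shift of at least half the effect (6.25 points) has probability at most 0.6% in every setting.

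**Step 6: randomization or analysis?** With stage also balanced at allocation, power of the stratified test in the six rows is 81.4, 82.2, 83.7, 85.8, 86.3 and 86.5%. That is within 1 point of the last column, so nearly all the gain comes from the analysis.

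**The case against.** **An adjusted analysis is already planned, and its covariates belong in the SAP.** This is the strongest objection, and part of it stands. The second-step model may well include stage, which is named under Covariables, and the SAP is not shown. That the article does not list the model's covariates is therefore no fault. The article does, however, put the unadjusted test first, sizes the trial on it and gives the model a verifying role. That ordering is stated, and it is what this point addresses. If the SAP already makes a stage-adjusted comparison the deciding one, the point is met.

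**The size rests on assumed inputs.** This stands. The documents give no stage mix and no rates by stage. A shift of a quarter to a third of the planned effect needs both a risk gap of 30–40 points and an imbalance near the 95% limit. The calculation also treats stage as unrelated to cancer type; balance on cancer type would remove some of the imbalance. The exclusion of patients permanently in inpatient care for a terminal condition would probably narrow the gap.

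**A reader might infer that the false-positive rate is inflated or the trial undersized.** The documents do not support either. Given one particular unlucky imbalance, the crude test does reject too often, but with stage balanced it rejects less than 5% of the time (2.9–4.7% in the same simulations), and over all randomizations the rate is about 5%. The planned 80% power is met.

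**A reader might also infer that stage must replace a randomization factor.** This does not follow. The gain is under 1 power point once the analysis is stratified, and the choice among reasonable factors is debatable. The Discussion also says recruitment began in November 2017 and ran six to nine months, so a change is probably too late. Planning subgroup analyses by stage does not oblige a trial to stratify allocation on it.

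**Conclusion.** The point holds as one of efficiency and interpretability, not of validity. The unadjusted test keeps its nominal error rate and its planned power, and 152 per group is right. Left as it is, the lead result carries whatever stage imbalance chance produces. At the 95% limit that is about 1 to 4.5 points of the planned 12.5 (7–36%); at a typical 1-SD imbalance it is 4–18%. A stage-stratified comparison corrects for that imbalance and raises power from about 81% to as much as 86–87% if stage is strongly prognostic. It loses essentially nothing if stage is weakly prognostic. All figures beyond the sample size depend on the assumed stage mix and risk gap.

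**What to change.** In the Primary endpoint paragraph under Statistics, or in the SAP, and before any outcome data are seen:

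1. Make the deciding primary comparison one stratified by stage group at entry: stages 0–III at first diagnosis versus stage IV, recurrent or metastatic. A Mantel-Haenszel risk difference with its confidence interval and the matching test would do.
2. Apply it to both ITT-1 and ITT-2.
3. Take stage from the entry physician form only, never from later restaging, and state how a patient with no stage on that form is classified.
4. Keep the unadjusted chi-square test as a supporting analysis.

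The randomization factors and the sample size stay as they are. The cost is a few lines of text: stage is already collected, and two strata raise no sparsity problem with about 340 patients. Timing is the one constraint, because stage adjustment added after results are known would look data-driven.

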**Fig. 1 Fig1:**
[figure not shown]
Study procedure. The figure shows the study flow from informed consent to randomization, intervention and analysis. Green arrows show personal contacts, black arrows any contact, dashed arrows optional contacts between study participants. M = month, R = randomization, t = time point#. Box colors: Green = patients, purple = physicians, blue = cancer patient navigators, orange = family members

### Study population

The study population comprises cancer patients who have been hospitalized at least once at one of the centers participating in the study as well as their relatives, outpatient and inpatient physicians, and cancer patient navigation program specialists. The inclusion and exclusion criteria for participation in the study must be observed.

Relatives of patients may be included regardless of their degree of relatedness, provided that they are of legal age and have declared their written consent to participate in the study. However, patients should nominate a close family member. Inclusion criteria for hospital physicians are that they must be employed at the hospital and have completed a good clinical practice course. Office-based physicians must be network partners of one of the participating hospitals. Participating cancer patient navigation program specialists must have successfully completed the SKG “Onkolotse” training course, have worked for at least two years in nursing at a cancer unit, and have cared for at least ten patients in their capacity as nurse navigation specialist prior to the study.

Neither the participating physicians nor the cancer patient navigation program specialists may have familiar relationships with the participating patients.

At least 340 cancer patients will be included in the study. The aim is to include not more than one family member per patient, although the exact number is not specified. Nor are the numbers of hospital-based and office-based physicians defined in advance.

### Inclusion criteria for patients

The patients must meet all of the following criteria to be included in the study:The patient is hospitalized at one of the five study centers.The patient has a diagnosis of gastric cancer, colonic/rectal cancer, pancreatic cancer, gynecological cancer, or melanoma.The patient has a cancer that falls into one of the following UICC TNM classifications:0 (t in situ, N0, M0)Ia (T1, N0, M0)Ib (T2, N0, M0)IIa (T3, N0, M0)IIb (T4, N0, M0)IIIa (every T, N1, M0)IIIb (every T, N2, M0)IV (every T, every N, M1)

or has a recurrent tumor or metastases (in the case of melanoma, also metastases that do not affect the skin).The patient is at least 18 years old.The patient has signed the written informed consent form.The patient participates in the study voluntarily.

